**Methods:**

Eligible subjects will be randomly divided into treatment group and control group in 1:1 ratio. Treatment group will receive CRF along with certain pre-defined CM according to symptoms for 8 weeks, while control group will receive equivalent packs of placebo for 8 weeks. Data in terms of Fatigue Severity Score (FSS), self-reported COVID-19 long term symptom assessment, the modified British Medical Research Council (mMRC) Dyspnoea Scale, EuroQol Five-Dimension Five-Level (EQ-5D-5L) Questionnaire, pulmonary function test and adverse events will be collected and analyzed by SPSS 24. Blood test on liver and renal functions will also be conducted as safety measures.

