### 4.2. Secondary outcomes

1.Self-reported COVID-19 Long Term Symptom Assessment at week 8.2.Improvement of fatigue using Fatigue Severity Score (FSS) at week 12.3.Change of modified British Medical Research Council (mMRC) dyspnoea scale to measure the improvement of dyspnoea at week 8 and 12.4.Change of EuroQol five-dimension five-level (EQ-5D-5L) questionnaire and it’s Visual Analogue Scale (VAS) to measure the quality of life at week 8 and 12.5.Improvement of pulmonary function FEV1, FVC, and FEV1/FVC ratio at week 8.6.Adverse events related to study treatment.

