### 7.3. Follow-up visit

Subjects will return for follow-up at week 8 (±4 days), and followed by a post-treatment visit at week 12 (Table 1). Symptom assessment and other questionnaires will be done. Blood tests will be repeated as safety measures at week 8. Subjects will be arranged to have another SARS-Cov-2 RT-PCR test of deep throat saliva/professional-administered combined nasal and throat swab, and confirmed to have negative medical and travel history related to COVID-19 within 72 h before the pulmonary function test at week 8. Performing deep throat saliva/professional-administered combined nasal and throat swab test and pulmonary function test are not mandatory. Treatment compliance will be recorded and adverse events will be captured on a patient diary. A direct telephone line will be provided so that subjects can report any adverse events during office hours between scheduled visits. The subjects will be recommended to attend Emergency Department at the nearest hospital beyond office hours if deemed necessary. To monitor compliance, subjects will be asked to bring back all remaining packs of granules for counting. One time free consultation with 1 month Chinese herbal treatment will be provided to all subjects after completion of study to ensure the follow up visit compliance.

**TABLE 1 T1:** Study schedule.

Items	Screening	Treatment period		Post-treatment follow up
	≤7 days to 0 day	Day 0 (baseline)	Week 8 (±4 days)	Week 12 (±4 days)
Informed consent	X			
Eligibility	X	X		
Medical consultation and assessment		X	X	X
Medical history		X		
Concomitant medication		X	X	X
Blood for safety measures	X		X	
Deep throat saliva or nasopharyngeal swab for SARS-Cov-2 RT-PCR test	*X		*X	
AE/SAE assessment			X	X
Questionnaires		X	X	X
Pulmonary function test		^#^X	^#^X	
Administration of study drug		X	X	
	

*Subjects will have deep throat saliva or nasopharyngeal swab for SARS-Cov-2 RT-PCR test within 72 h before follow up visit but it is not mandatory.

^#^Pulmonary function test will be skipped if no deep throat saliva has been done and showed not detected or negative within 72 h.

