#### 7.4.6. Blood test

Venous blood samples will be collected from all participants for hematology, liver and renal function tests as safety measures.

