### 9.2. Adverse events

An adverse event is any undesirable medical event occurring in the subject within the trial period, whether or not it is related to the study intervention. No serious adverse event has been reported of taking COVID-19 Rehabilitation Formula (CRF). The adverse reaction will be recorded and the treatment will be suspended when severe adverse reaction occurs. The assessment of adverse event will be recorded according to CTCAE 4.0 which is a standard assessment tool.

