### 10.2. Statistical analysis

Baseline data (gender, age, and vital signs) will be descriptively summarized. Differences of measurement data between the groups will be assessed using *t*-test for normally distributed continuous variables and Wilcoxon signed rank test for non-normally distributed variables. Measurement data of different groups in each visit will be reported as mean ± standard deviation (SD). Intra-group comparisons between baseline and each visit will be conducted by using paired *t*-test (or Wilcoxon signed rank test). Comparisons between groups will be conducted by using an analysis of variance (ANOVA), with other confounding factors like multicenter character conducting the covariate analysis. Statistical analysis for the data which do not meet above conditions (e.g., non-normal) will be conducted with the use of non-parametric test. For laboratory parameters, Spearman’s coefficient correlation has been used for comparison with different parameters and one way ANOVA test for significant correlation between groups. Study flow chart and graphs will be presented over different study times.

All *p*-values and 95 percent confidence intervals are two-sided, and *p* < 0.05 is considered statistically significant. Statistical analyses will be carried out exclusively by an independent statistician. All analyses will be performed by using SPSS, version 24 (SPSS).

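### The laboratory analysis sentence names methods that do not serve the safety purpose of the bloods, and secondary outcome 6 is narrower than the protocol's own adverse event definition

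*Protocol article*

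**What the plan says.** - **Purpose and timing of the bloods.** Section 7.4.6: "Venous blood samples will be collected from all participants for hematology, liver and renal function tests as safety measures". Section 7.3: "Blood tests will be repeated as safety measures at week 8". Table 1 shows two draws, at screening and at week 8.
- **Analysis of the bloods.** Section 10.2 gives laboratory parameters their own sentence, in which Spearman's "coefficient correlation has been used for comparison with different parameters and one way ANOVA test for significant correlation between groups". That sentence mentions no change from screening and no summary of abnormal values.
- **Other analysis text.** The same section plans, for measurement data in general, mean ± SD by group and visit, paired within-group tests against baseline, a between-group ANOVA with covariates, and a non-parametric fallback. It does not say whether these also apply to laboratory values.
- **Adverse event outcome.** Section 4.2, item 6: "Adverse events related to study treatment".
- **Adverse event definition and grading.** Section 9.2 defines an adverse event as any undesirable medical event in the trial period, "whether or not it is related to the study intervention", and adds: "The assessment of adverse event will be recorded according to CTCAE 4.0 which is a standard assessment tool".
- **Abstract, Methods.** It lists "pulmonary function test and adverse events will be collected and analyzed by SPSS 24", with no restriction to related events.

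**The concern.** The abstract promises an evaluation of safety as well as efficacy. For the bloods, the safety question is whether values move more under CRF than under placebo, and whether individual patients become abnormal. Patients with impaired liver or renal function are excluded at entry (section 6.2), so a new abnormality at week 8 is the signal of interest. The laboratory sentence addresses neither part clearly. One of its methods cannot answer the question, and the other is described as testing something it does not test. An analyst who followed the sentence literally could report a non-significant result as evidence of safety when the method had little chance of showing a problem limited to a few patients.

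The adverse event text raises a second question: which events make up the outcome? If only related events are tabulated, the result depends on a causality judgement that the protocol's own definition does not require.

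**Working it through.** **1. Patients per arm.** Section 10.1 gives a difference of 9, SD 12, two-sided alpha 0.05 and power 0.80. The standardised difference is 9/12 = 0.75. The t-based calculation needs 28.9, so 29 per arm or 58 in total, which reproduces the protocol's figure. The protocol randomises 34 per arm after allowing for dropout. The safety comparison therefore has about 29 to 34 patients per arm.

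**2. What Spearman's coefficient can show.** It depends only on ranks. In a simulated set of 34 patients with correlated ALT and AST, rho was 0.818. After every value was tripled it was still 0.818. A threefold rise in a whole arm leaves the within-arm coefficient unchanged, so it carries no information on a shift.

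**3. What the ANOVA can show.** With two groups, one-way ANOVA is the pooled t-test. On simulated data F = 6.8995 and t² = 6.8995. It tests a difference in means, so it can detect a general shift. It does not test correlation, and in its one-way form it does not use the screening value.

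**4. A rise confined to k patients.** The documents give no laboratory values, so all ALT inputs here are assumptions.

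*Model A:* 29 per arm, ALT normal with mean 25 and SD 8 U/L. In the CRF arm, k values come from a normal with mean 160 and SD 20, so D = 160 − 25 = 135.
- Mean difference = kD/n.
- CRF-arm variance = [within + D²(k/n)(1 − k/n)] × n/(n − 1), where within = [(n − k)·8² + k·20²]/n.
- t ≈ (kD/n) / √[(CRF variance + 64)/n], against a critical value of 2.003 on 56 df.

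For k = 2:
- difference = 270/29 = 9.31
- within = (27·64 + 2·400)/29 = 87.2
- between = 18,225 × (2/29)(27/29) = 1,170.2
- variance = 1,257.4 × 29/28 = 1,302, so SD 36
- t ≈ 9.31/√(1,366/29) = 1.36

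The same steps give t ≈ 1.72 for k = 3 and 2.04 for k = 4. The affected patients inflate the variance that the test divides by, so t stays below the critical value until k = 4.

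*Model B:* 29 or 34 per arm, ALT log-normal with median 22 and log-SD 0.4. In the CRF arm, k values are multiplied by 5. The test is run on the raw and the log scale.

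Simulated proportion of trials with p < 0.05:

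| CRF patients affected | Model A | Model B |
|---|---|---|
| 1 | 0.6% | 3–5% |
| 2 | 2.1% | 5–8% |
| 3 | 14.1% | 13–15% |
| 4 | 56% | 22–31% |

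The models agree closely for 3 patients, broadly for 2, and not for 4.

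**5. Would a test on counts do better?** Fisher's exact test with 29 to 34 per arm gives p = 0.49 for 2 v 0, 0.24 for 3 v 0, 0.11 for 4 v 0, 0.052–0.053 for 5 v 0 and 0.023–0.025 for 6 v 0. It does not fall below 0.05 until 6 v 0. Counts help because they display the cases, not because they test them.

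**6. Adverse event texts side by side.** Section 4.2 restricts the outcome to related events. Section 9.2 defines events regardless of relatedness and grades them by CTCAE. The abstract has adverse events analysed without restriction. Recording is therefore wide, and the outcome list is narrower than both other statements.

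**The case against.** A reader might infer that real liver or renal harm would go unseen. The documents do not support that, for these reasons:

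- **The ANOVA is usable.** Despite its description, it is a valid comparison of two means, so a general shift would be tested.
- **Other text may apply.** The generic mean ± SD summaries and paired tests in section 10.2 may extend to laboratory data. Under Model A with 2 affected patients, the CRF arm would show about 34 ± 36 against 25 ± 8, which is conspicuous even though it does not identify the patients.
- **Individual toxicity has another route.** The definition in section 9.2 is wide enough to include a marked laboratory rise, and events are CTCAE-graded. The section does not say that abnormal bloods are logged as events, but it does not exclude them.
- **The low power is mostly a matter of trial size.** No significance test would reliably find 2 or 3 cases in about 30 per arm.
- **Detailed safety tables usually belong in the SAP**, which is not shown.

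A reader might also infer that unrelated adverse events are not collected. Section 9.2 shows that they are. Causality is judged in a double-blind trial, so the restriction does not by itself imply bias between arms.

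All of this limits the point. What it leaves standing is that the article gives laboratory parameters a specific rule and states it wrongly, which is not the same as leaving detail to the SAP. The generic paired tests are within-group averages, so they neither compare the arms nor identify individuals. Three statements about adverse events still disagree.

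**Conclusion.** The point holds as a misstated method plus an inconsistency, both confined to safety reporting. Spearman correlation between parameters cannot show whether CRF changes liver, renal or haematology values, and ANOVA is described as testing something it does not test. That much is certain and needs no assumption. The chance that the ANOVA flags a rise limited to a few patients is low, about 2–8% for 2 patients and 13–15% for 3. Those figures rest on assumed ALT distributions and assumed sizes of rise, and should be read as illustrative. Secondary outcome 6 conflicts with section 9.2 and the abstract on which adverse events are analysed. The FSS analysis, the sample size and the efficacy conclusions are untouched.

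**What to change.** 1. Delete the Spearman and correlation sentence from section 10.2.
2. Compare the arms on change from screening to week 8 for each laboratory parameter, adjusted for the screening value, with a 95% confidence interval.
3. Describe, by arm, the number of patients with abnormal or CTCAE-graded liver, renal and haematology values. CTCAE 4.0 is already adopted in section 9.2. State that these counts are descriptive, and that a non-significant difference is not evidence of safety.
4. Reword secondary outcome 6 to all adverse events by arm, with treatment-related events as a subset, so that section 4.2, section 9.2 and the abstract agree.

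The cost is a change of wording and a few tables. No new data, visits or patients are needed.

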## 11. Ethics consideration

Application for ethical approval have been sought from Joint CUHK-NTEC CREC before the initiation of this study. All important protocol modifications are approved by the said CREC before implementation (except in emergency situations where immediate hazards to the subjects have to be eliminated) and communicated to investigators, research personnel and trial participants. Participants are informed of our measures to ensure the confidentiality of all information and that data are maintained anonymous. Investigators/research personnel obtain informed consents from subjects and consent forms are signed by the subjects before the study. All information are encrypted and only the involved investigators can access. Password is required to access the data. Participants are free to withdraw at any time without giving a reason or punishment. The personal data of the subjects will only be kept for 10 years and will be destroyed afterward.

## 12. Clinical trial insurance

Clinical trial insurance will be purchased according to the university policy.

## 13. Quality assurance

### 13.1. Data management

Only the study team and the PI have access right to the database using their login user names and passwords. Subjects’ information is kept anonymous. They are identified by their study numbers to maintain subjects’ confidentiality. The final dataset of the study will be available from the corresponding author on reasonable request.

### 13.2. Auditing and inspection

The Clinical Research Management Office at The Chinese University of Hong Kong or an external auditor will perform auditing or inspection to determine whether research activities are conducted according to the protocol, Good Clinical Practice (GCP) and guidelines of the International Conference on Harmonization (ICH).

## 14. Dissemination policy

We will communicate the results mainly through scientific publications and/or press conferences. No publication restrictions are planned. Authorship will be determined based on the criteria adopted by the International Committee of Medical Journal Editors.

## Ethics statement

Approval (reference number: 2021.125-T) has been obtained from The Joint Chinese University of Hong Kong—New Territories East Cluster Clinical Research Ethics Committee. Informed consent will be signed before subject enrolment. The results will be submitted to peer-reviewed journals and presented at academic conferences.
